### Planned statistical analyses

It has been shown that the 5-year BPFS rate ranges from 63% to 98% in patients with intermediate-risk PCa who undergo radiotherapy [13,14]. Assuming that the 7-year BPFS rate of the control group is 60% (the 5-year BPFS is about 69%) and the expected 7-year BPFS rate of the adjuvant ADT group is 73.6% (i.e. hazard ratio is 0.6), 190 patients for each group are needed to detect a significant difference between treatments by log-rank test with a significance level of 0.05 and a power of 80%. Given the further assumption that approximately 10% of randomized patients will be unevaluable for various reasons, the target sample size was set at 210 patients per group (420 patients total).

Statistical analyses will be performed on an intention-to-treat basis. Survival curves will be estimated using the Kaplan-Meier method. To test for differences in survival curves between the two groups of patients, the log-rank test will be used. The hazard ratio will be estimated using the Cox proportional hazard model. The longitudinal change of QOL scores (IPSS, SF-8, and EPIC) between diagnosis and 60 months following ^125^I-TPPB will also be compared between groups. Patients will be evaluated for toxicity, graded according to the National Cancer Institute Common Toxicity Criteria version 3.0 [15]. For all patients, the incident proportion of grade 3 adverse events will be compared between groups by Fisher exact test. All tests will be two-sided, and a value of 0.05 will be considered statistically significant. Five years after the last patient is recruited, an interim analysis will be performed and the results will be reported to the Independent Data Monitoring Committee.

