**Methods/Design:**

Seed and Hormone for Intermediate-risk Prostate Cancer (SHIP) 0804 is a phase III, multicenter, randomized, controlled study that will investigate the impact of adjuvant ADT following neoadjuvant ADT and ^125^I-TPPB. Prior to the end of March, 2011, a total of 420 patients with intermediate-risk, localized PCa will be enrolled and randomized to one of two treatment arms. These patients will be recruited from 20 institutions, all of which have broad experience of ^125^I-TPPB. Pathological slides will be centrally reviewed to confirm patient eligibility. The patients will initially undergo 3-month ADT prior to ^125^I-TPPB. Those randomly assigned to adjuvant therapy will subsequently undergo 9 months of adjuvant ADT. All participants will be assessed at baseline and at the following intervals: every 3 months for the first 24 months following ^125^I-TPPB, every 6 months during the 24- to 60-month post-^125^I-TPPB interval, annually between 60 and 84 months post-^125^I-TPPB, and on the 10th anniversary of treatment.

The primary endpoint is biochemical progression-free survival (BPFS). Secondary endpoints are overall survival (OS), clinical progression-free survival, disease-specific survival, salvage therapy non-adaptive interval, acceptability (assessed using the international prostate symptom score [IPSS]), quality of life (QOL) evaluation, and adverse events. In the correlative study (SHIP36B), we also evaluate biopsy results at 36 months following treatment to examine the relationship between the results and the eventual recurrence after completion of radiotherapy.

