### Methods of recruitment and random allocation

Recruitment of patients is supported by the Seed and Hormone for Intermediate-risk Prostate Cancer Study Group (SHIP). Recruiting began in April, 2008, and is planned for completion by March, 2011. Initial recruitment is through the secretariat division of SHIP. All prostatic biopsy histological slides of newly diagnosed PCa since the study was initiated have been reviewed by central pathologists, with patient eligibility being determined at the time of review. Eligible patients are randomly assigned to one of two treatment arms through the data center at the TRI. Randomization is done centrally using a minimization method to obtain good between-group balance for factors including age category (< 70/≥ 70), PSA category (< 10/≥ 10 ng/mL) and institutions.

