### Definition of endpoints

The primary endpoint is biochemical progression-free survival (BPFS). Biochemical progression is defined as an increase in prostate specific antigen (PSA) of 2 ng/mL or greater from the nadir value following treatment. Secondary endpoints include OS, clinical progression-free survival (local, distant failure), disease-specific survival, salvage therapy non-adaptive interval, acceptability (assessed by the international prostate symptom score [IPSS]), quality of life (QOL) and adverse events. Overall survival and progression-free survival are respectively calculated from the 1st day of treatment to any death, or to identification of disease progression or death. Local progression is defined as reappearance of local tumorat the primary site. Reappearance of local tumor will be confirmed by rectal examination and imaging studies such as magnetic resonance imaging or computed tomography. The primary endpoint of a correlative study (SHIP36B) is the biopsy results at 36 months following treatment to examine the relationship between results and eventual recurrence after completion of radiotherapy.

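### Minimisation on age, PSA and institution is not carried into the primary log-rank test and Cox model, which makes the analysis mildly conservative if those factors are prognostic

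*Protocol article*

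**What the plan says.** On allocation, the protocol article's section on recruitment and random allocation says "Randomization is done centrally using a minimization method to obtain good between-group balance for factors including age category", with cut-points at age 70, and goes on to "PSA category (< 10/≥ 10 ng/mL) and institutions". The abstract gives the number of centres: "These patients will be recruited from 20 institutions".

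On analysis, the section on planned statistical analyses says "To test for differences in survival curves between the two groups of patients, the log-rank test will be used" and "The hazard ratio will be estimated using the Cox proportional hazard model". It names no strata and no covariates for either. The sample size in the same section is for a log-rank test at a two-sided 0.05 level and 80% power. It assumes 7-year BPFS of 60% against 73.6% (hazard ratio 0.6), which gives 190 per group and 210 after an allowance for unevaluable patients.

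**The concern.** Minimisation makes the two arms agree on the chosen factors more closely than simple randomisation would. If those factors predict BPFS, the treatment comparison varies less from one possible allocation to the next than the ordinary log-rank variance supposes. A test that leaves the factors out then divides by too large a standard error, so it rejects less often than its nominal level and gives up some power. Carrying the factors into the analysis brings the variance back into line with the design.

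Efficiency that needs no extra patients is useful here, because the article reports enrolment below goal (181 of 420 by December 2009). At stake is a modest amount of precision, together with the need to fix the form of the primary test before outcomes are compared.

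**Working it through.** **1. The plan's own figure.** Inputs are from the section on planned statistical analyses.
- Hazard ratio: ln(0.736)/ln(0.6) = 0.600, as stated.
- Freedman events: (1.960 + 0.842)² × ((1 + 0.6)/(1 − 0.6))² = 7.85 × 16 = 125.6, so 126.
- Mean 7-year event probability: 1 − (0.600 + 0.736)/2 = 0.332.
- Patients: 126/0.332 = 379.5, so 190 per group. This matches the article.
- Schoenfeld's formula gives 121 events and 182 per group, which does not match.

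Both formulas are for a plain two-group log-rank test, so no gain from stratification entered the sample size.

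**2. Size and power under minimisation.** The documents give no prognostic strengths, so four settings were assumed, each written as age hazard ratio / PSA hazard ratio / standard deviation of the centre log-hazard:
- none: 1 / 1 / 0
- moderate: 1.2 / 1.5 / 0.2
- strong: 1.3 / 2.0 / 0.4
- very strong: 1.5 / 3.0 / 0.5

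Further assumptions were 380 patients, 20 centres of equal expected size, 50% aged 70 or over, 40% with PSA of 10 or more, biased-coin minimisation with probability 0.8, and 7 years of follow-up for everyone. Marginal control 7-year BPFS was held at 60%, and the treatment hazard ratio of 0.6 was conditional on the factors. There were 8,000 simulated trials per cell, and all tests were applied to the same trials.

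Type I error (nominal 0.05):

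| Setting | Unstratified | Age × PSA (4 strata) | All factors (80 strata) |
|---|---|---|---|
| None | 0.052 | 0.052 | 0.049 |
| Moderate | 0.047 | 0.049 | 0.049 |
| Strong | 0.042 | 0.047 | 0.051 |
| Very strong | 0.033 | 0.044 | 0.054 |

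Power (%):

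| Setting | Unstratified | 4 strata | Difference | 80 strata | Difference |
|---|---|---|---|---|---|
| None | 81.5 | 81.0 | −0.5 | 71.5 | −10.0 |
| Moderate | 80.2 | 80.4 | +0.2 | 71.1 | −9.1 |
| Strong | 77.7 | 78.9 | +1.2 | 70.0 | −7.7 |
| Very strong | 73.8 | 77.9 | +4.1 | 68.9 | −4.9 |

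Differences are from the unstratified test. A Cox model with age and PSA as covariates behaves like the four-stratum test (power 81.3, 80.5, 79.0 and 78.2%).

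The Monte Carlo standard error is about √(0.05 × 0.95/8000) = 0.0024 for size and √(0.8 × 0.2/8000) = 0.45 points for power. The moderate figure of 0.047 is therefore about one standard error below 0.05 and not clearly different from it. The strong and very strong figures are clearly below.

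A separate simulation with exact balance on age × PSA and no centre effect points the same way. With a PSA hazard ratio of 2, size was 4.4% unstratified against 4.9% stratified, and power 80.3% against 81.9%. With a ratio of 3, size was 3.5% against 5.0%, and power 79.1% against 82.7%. With a ratio of 1.5 there was no material difference.

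**3. Why not cross in institution.** Four age × PSA cells times 20 institutions is 80 strata. That is 380/80 = 4.75 patients and about 126/80 = 1.6 events per stratum. Many events then fall where everyone still at risk is in one arm, and these contribute nothing. This explains the loss of about 5 to 10 points.

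**The case against.** The strongest objection is that the article does not say the analysis is unstratified. It names a type of test, and strata or covariates are often set in the full protocol or analysis plan, which is not shown. This stands as a caution. The reading rests on the named test together with a sample size that fits a plain log-rank test, so it is the natural one but not a certain one.

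A reader might infer that the plan throws away power it has already paid for. The documents do not support that: the 190 per group was derived for the plain test, so no adjustment gain was budgeted. Nor do the simulated powers of 77.7% and 73.8% show a shortfall against the stated design. They set the hazard ratio of 0.6 conditional on the factors, whereas the article derives 0.6 from marginal 7-year rates. For the same reason the unadjusted hazard ratio is not wrong; it answers a marginal question.

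A reader might also take PSA to be strongly prognostic because it defines risk groups. Within this cohort that cannot be presumed. The eligibility criteria exclude low-risk disease, so a patient with PSA below 10 must qualify by Gleason score or stage, while one above 10 need not, and PSA is capped at 20. This selection may blunt the contrast between PSA categories.

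Finally, four strata leave institution, itself a minimisation factor, out of the test. That is true, and it is probably why the four-stratum size stays slightly low (0.044) in the very strong setting. Crossing it in is much more costly than leaving it out.

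**Conclusion.** The point holds as a minor, low-cost improvement. As written, the primary analysis does not reflect the factors used in allocation. If those factors are prognostic, the unstratified test is mildly conservative: type I error is about 0.047 to 0.042 at moderate to strong effects and 0.033 at very strong effects. If they are not prognostic there is no conservatism (0.052). The power forgone is about 0 to 1 point, rising to about 4 points only under very strong effects.

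The error is in the safe direction, so the validity of the primary test is not threatened, and the planned 80% power did not depend on adjustment. The sizes rest on the assumed prognostic strengths, prevalences and minimisation probability, none of which the article gives.

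**What to change.** State in the analysis section that the primary log-rank test is stratified by age category × PSA category (four strata), and that the hazard ratio comes from a Cox model with the same strata. Report the unstratified test and hazard ratio as supportive. Do not stratify by institution; examine it in a sensitivity analysis, for example as a random effect in the Cox model. Fix this before the interim analysis planned five years after the last patient is recruited, and use the same test there. If the full plan already says this, confirming it is enough. Adding Gleason score and T stage to the model is optional and not needed for this point.

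The change needs no further patients or visits, since age and PSA category are already recorded at randomisation. Its price is about half a point of power if the factors turn out not to be prognostic (81.5% to 81.0%), and a hazard ratio that must be read as conditional on the strata. The sample size need not change.

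### The between-arm test of graded toxicity is defined on grade 3 events without "or higher", so read literally it leaves out patients whose only severe event is grade 4 or 5

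*Protocol article*

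**What the plan says.** Definition of endpoints in the protocol article lists adverse events among the secondary endpoints, next to symptom score and quality of life: "acceptability (assessed by the international prostate symptom score [IPSS]), quality of life (QOL) and adverse events". Planned statistical analyses then names the grading scale: "Patients will be evaluated for toxicity, graded according to the National Cancer Institute Common Toxicity Criteria version 3.0". The next sentence sets the comparison, for all patients: "the incident proportion of grade 3 adverse events will be compared between groups by Fisher exact test". The error rate is general: "All tests will be two-sided, and a value of 0.05 will be considered statistically significant".

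So the category (grade 3), the summary (a proportion), the test (Fisher), the sidedness and the level are all fixed. The category has no upward extension, and no other section analyses grade 4 or grade 5 events as toxicity.

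**The concern.** The named scale has two grades above 3: grade 4 for life-threatening events and grade 5 for fatal ones. (This is a property of the scale; the article does not print it.) A comparison restricted to grade 3 therefore covers severe events but omits the more serious ones. A patient with no grade 3 event and one grade 4 event would sit in the no-event cell of the Fisher table.

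Such a count also does not rise steadily with harm. If an event worsens from grade 3 to grade 4 and is recorded only at its worst grade, the patient leaves the numerator, so more serious toxicity could look like less.

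This matters because the Background argues that adjuvant ADT has an adverse-event cost and that recommending it should wait for firmer evidence of benefit. The abstract's Discussion promises safety data. The graded comparison is one of the tools meant to supply them.

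**Working it through.** **1. Is the category widened anywhere?** The places that deal with adverse events are the abstract, the Background, Definition of endpoints, Planned statistical analyses and the Discussion. Only Planned statistical analyses names a grade, and it says 3. Elsewhere the article marks a threshold when it means one: the Gleason and stage criteria for high risk carry ≥, and biochemical progression is a rise of 2 ng/mL or more from nadir. The missing extension therefore cannot be put down to a general habit of dropping such marks.

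**2. Is there a planned figure to reproduce?** Not for toxicity: no rate, difference or power is stated. The 80% power belongs to the primary log-rank test. That sample size does reproduce and is not affected:
- Freedman events at hazard ratio 0.6, two-sided 0.05, power 80%: 126.
- Mean 7-year event probability: 1 − (0.60 + 0.736)/2 = 0.332.
- Patients: 126/0.332 = 379.5, or 189.8 per arm, against the stated 190.

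The stated 210 randomized per arm is used as the denominator below.

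**3. What could the wording do?** All counts here are assumed. Let a be the patients in an arm with a grade 3 event, and b those whose only severe event is grade 4 or 5. The literal rule uses a/210; grade 3 or higher uses (a + b)/210. P values are two-sided Fisher.

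| Adjuvant a + b | Control a + b | Grade 3 only | p | Grade 3 or higher | p |
|---|---|---|---|---|---|
| 14 + 4 | 6 + 0 | 6.7% v 2.9% | 0.107 | 8.6% v 2.9% | 0.019 |
| 10 + 5 | 4 + 1 | 4.8% v 1.9% | 0.172 | 7.1% v 2.4% | 0.037 |
| 12 + 6 | 8 + 2 | 5.7% v 3.8% | 0.493 | 8.6% v 4.8% | 0.170 |
| 12 + 6 | 12 + 0 | 5.7% v 5.7% | 1.00 | 8.6% v 5.7% | 0.34 |

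In the first two rows the result crosses 0.05. In the last two it is non-significant either way, although the last row turns an observed difference into none.

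**4. Effect on power, again with assumed rates.** Suppose the true proportions with grade 3 or higher are 10% v 4%. Exact Fisher power at 210 per arm is 62% when all affected patients count. If 10%, 20% or 30% of the affected patients in each arm have only grade 4 or 5 events and are left out, power falls to 56%, 50% or 44%.

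**The case against.** The strongest reply is that this is loose wording in a condensed article. The preceding sentence applies the whole scale without restriction, nothing expressly excludes grades 4 and 5, and the article is careless with qualifiers elsewhere: the inclusion criteria print creatinine and transaminase limits with ≥ under a requirement for appropriate organ function. The full protocol may well say grade 3 or higher. This stands as a reason not to read the phrase as a deliberate decision to ignore the worst events. It does not remove the defect: the article states the category rather than leaving it open, and an analyst who followed it would get the wrong table.

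Three stronger readings are tempting, and the article does not support them:

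- *Deaths would be hidden.* They would not. Overall survival counts any death, disease-specific survival is also an endpoint, and follow-up records survival. What is lost is fatal toxicity as part of the toxicity comparison.
- *This is the only safety comparison.* It is the only one of graded adverse events. IPSS, SF-8 and EPIC scores are also compared between arms up to 60 months, and the Discussion says adverse effects will be assessed by questionnaire. Most of the ADT harms named in the Background are of the kind those instruments address.
- *The toxicity conclusion would be reversed.* No rates are given, so nothing shows that it would. A patient with a grade 4 or 5 event who also had a separate grade 3 event is still counted, which narrows the affected group.

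**Conclusion.** The point holds as a defect in the stated definition of one secondary comparison. It rests on the literal wording, on the absence of any widening text, and on the named scale having grades above 3. If grade 3 or higher was intended, the sentence is wrong as printed; if not, the test omits the most serious toxicity.

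The size is unknown. It depends on how many patients have only grade 4 or 5 events and in which arm. As few as four such patients moved p from 0.107 to 0.019 under one set of assumed counts; other sets changed no conclusion. The primary endpoint, the sample size and the survival analyses are untouched. The change should be made, but the trial's main result does not depend on it.

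**What to change.** Reword the sentence along these lines: the proportion of patients with at least one adverse event of grade 3 or higher (worst grade per patient) will be compared between groups by Fisher exact test. Add that grades 3, 4 and 5 will be tabulated separately by arm, so that life-threatening and fatal toxicity can be seen and not only pooled.

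The cost is a short text change and one extra table. Toxicity is already to be graded on the named scale, so no new data, patients or visits are needed. If the full protocol or analysis plan already says grade 3 or higher, the article's sentence need only be brought into line with it.

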### Patient enrollment and anticipated completion of enrollment

Monthly enrollment was moderately below goal, but cumulative enrollment reached 181 cases in December, 2009. Slow enrollment may reflect the relatively low frequency of PCa patients with intermediate-risk [4]. Our current expectation is that the final patient will be enrolled by March, 2011; the study will be clinically complete by 2021 and results will be available during the first quarter of 2022.

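### Reported accrual does not fit 420 patients by March 2011; either the recruitment and March 2021 dates or the stated size and power need restating

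*Protocol article*

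**What the plan says.** The Abstract (Methods/Design) sets the target and the date together: "Prior to the end of March, 2011, a total of 420 patients with intermediate-risk, localized PCa will be enrolled". The section on recruitment and random allocation gives the window: "Recruiting began in April, 2008, and is planned for completion by March, 2011". Planned statistical analyses derives the 420 from 190 evaluable patients per group, for 80% power on 7-year biochemical progression-free survival (BPFS) of 60% against 73.6% (hazard ratio 0.6), with about 10% unevaluable.

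The section on patient enrollment then reports progress: "Monthly enrollment was moderately below goal, but cumulative enrollment reached 181 cases in December, 2009". It suggests that intermediate-risk patients are relatively uncommon, and continues: "Our current expectation is that the final patient will be enrolled by March, 2011". The same paragraph expects clinical completion by 2021 and results in the first quarter of 2022.

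Three other statements bear on the dates. Data collection ends the active phase, and with it annual follow-up, in March 2021. The Abstract plans an assessment at the 10th anniversary of treatment, and the Discussion names 10-year BPFS as the primary goal. Planned statistical analyses places the interim analysis five years after the last patient is recruited.

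**The concern.** The accrual figure and the completion date appear in the same paragraph and do not fit together. The article says enrolment is behind, gives a cause that will not resolve itself, names no countermeasure (added sites, a longer window or a smaller target), and leaves the date unchanged.

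What is at stake depends on what gives way. If the target of 420 is kept, recruitment runs past March 2011 and the calendar end of follow-up cuts short the 10-year observation of the later patients. If the date is kept, the trial closes below its planned size and the stated 80% no longer describes it.

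**Working it through.** **Inputs from the article.** Recruitment April 2008 to March 2011, 36 months; target 420; 181 enrolled in December 2009, taken as month 21; 7-year BPFS 60% and 73.6%; hazard ratio (HR) 0.6; two-sided 0.05; power 80%; 10% unevaluable; 3 months of hormone therapy before implant; follow-up ends March 2021.

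**1. The plan's own sample size.** Freedman's formula gives events = (1.96 + 0.84)² × [(1 + 0.6)/(1 − 0.6)]², which rounds up to 126. The mean 7-year event probability is (0.400 + 0.264)/2 = 0.332. Then 126/0.332 = 379.5, or 190 per group, which matches the article. Schoenfeld's formula gives 121 events and 183 per group. The plan therefore fits Freedman with 7 years of follow-up counted for everyone.

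**2. Accrual.**
- Average planned pace: 420/36 = 11.7 per month, so 245 by month 21 if spread evenly (the article states no monthly goal).
- Achieved: 181/21 = 8.6 per month; 181/245 = 74%.
- Needed: (420 − 181)/15 = 239/15 = 15.9 per month. That is 15.9/8.62 = 1.85 times the achieved rate and 15.9/11.67 = 1.37 times the average planned pace.
- Constant rate to March 2011: 8.62 × 36 = 310. Taking 20 or 21 months elapsed and 14 to 16 remaining gives 302 to 326.
- Full average planned pace from January 2010: 181 + 15 × 11.67 = 356.
- Time to 420 at the achieved rate: 420/8.62 = 48.7 months, about April 2012.

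**3. If recruitment continues to 420.** With 3 months before implant, men enrolled after December 2010 (month 33) reach their 10th implant anniversary after March 2021.
- At the achieved rate: 420 − 33 × 8.62 = about 136 men, 136/420 = 32%.
- On schedule: 3 × 11.67 = about 35 men.
- Attributable to slow accrual: 136 − 35 = about 101.
- The last implant would fall about July 2012, with a 10th anniversary about July 2022.

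**4. If recruitment closed in March 2011.** Power (Freedman) = Φ(√events × (1 − HR)/(1 + HR) − 1.96), with Schoenfeld as a check.

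| Enrolled | Evaluable (×0.9) | Events at 7 years (×0.332) | Power, Freedman | Power, Schoenfeld |
|---|---|---|---|---|
| 420 | 378 | 125.5 | 80% | 82% |
| 356 | 320 | 106 | 73% | 75% |
| 310 | 279 | 93 | 67% | 69% |

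For 310: √92.6 × 0.25 − 1.96 = 0.446, and Φ(0.446) = 0.672. Over 302 to 326 enrolled the Freedman figure runs from 66% to 69%.

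**5. The same numbers with all follow-up to March 2021.** Assume constant hazards λ = −ln(0.6)/7 in control and 0.6λ with adjuvant therapy, uniform accrual over a = 3 years, and f = 10 years after the last enrolment. For hazard h, the event probability is 1 − [exp(−hf) − exp(−h(f + a))]/(ha), averaging 0.481 over the groups. With 279 evaluable this gives 134 events and power of 82% (Freedman) to 84% (Schoenfeld). With 420 enrolled (378 evaluable) it gives 182 events and 92% to 93%.

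**The case against.** The fair defence is that this is a forecast in a status paragraph. It changes no endpoint, test or analysis rule, and a constant rate from the first month is pessimistic for 20 sites that start up gradually. Illustrative ramps (assumed, not in the article) show the effect. A linear 12-month start-up that fits 181 at month 21 implies a steady 181/(21 − 6) = 12.07 per month and 12.07 × 30 = 362 by March 2011. An 18-month start-up implies 181/(21 − 9) = 15.08 and 15.08 × 27 = 407. So 310 is a scenario and not a certainty. But neither ramp reaches 420, and both imply recent monthly enrolment above the average planned pace of 11.67. That sits badly with "Monthly enrollment was moderately below goal" and with the article's own remark on slow enrolment. The mismatch in dates stands.

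A reader might draw three stronger conclusions that the article does not support.
- *That power will fall to 67%.* No statement orders recruitment to close in March 2011 short of 420; the date is a plan and an expectation. If recruitment ran to April 2012, the last patient would still have about 8.7 years from implant by March 2021, beyond the 7-year sizing horizon. The 67% also counts only 7 years per patient. That is like for like with the stated 80%, but it is not the power of a log-rank test on all follow-up.
- *That the interim analysis depends on March 2011.* It is already set relative to the last patient recruited and moves with accrual.
- *That all 136 men are lost to slow accrual.* About 35 would pass March 2021 before their 10th implant anniversary even on schedule.

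It is also fair to say that later patients would be censored, not discarded. The cost in the first scenario is a truncated 10-year assessment and a less precise 10-year BPFS estimate, not an invalid comparison.

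**Conclusion.** The point holds as an inconsistency between reported accrual and the stated dates. Reaching 420 by March 2011 needs 1.85 times the achieved rate (1.65 times on the most favourable month count, 20 elapsed and 16 remaining). Even an immediate rise to the average planned pace stops at about 356. This part rests only on the article's figures and simple arithmetic.

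The consequences are alternatives, each conditional. With recruitment continued to 420, the 7-year power is kept, but about a third of the men would not complete 10 years from implant before follow-up ends; this assumes the achieved rate persists and 3 months from enrolment to implant. With recruitment closed in March 2011 at about 310, power is 67% to 69% on the plan's 7-year basis, or 82% to 84% with all follow-up to March 2021 under constant hazards and uniform accrual. A correction is worthwhile because the calendar end of follow-up determines whether the 10-year observation is complete.

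**What to change.** Choose one of two consistent sets of statements.

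- **Keep 420.** Restate the expected end of recruitment from observed accrual (about April 2012 at the constant rate, updated with the monthly figures the sponsor holds). Define the end of the active phase relative to the last patient's implant, long enough for the planned 10-year assessment, in place of March 2021. Move the completion and reporting dates accordingly. The cost is amended dates, longer follow-up, and final results about a year or more later than the first quarter of 2022.
- **Keep March 2011 and March 2021.** Restate the expected number enrolled and the power for that number, saying whether it counts 7 years per patient or all follow-up to March 2021, and state how many men will have a full 10 years from implant. The cost is a less favourable power figure.

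The interim analysis needs no change to its rule; only its expected calendar date moves.
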